## Abstract

**Background:**

In the last decade, alcohol consumption among middle-aged women (40-65 years old) in Australia increased, despite declines in overall population consumption. Web-based, brief interventions are promising for reducing alcohol consumption, with efficacy shown in a wide range of populations. However, no published interventions have been designed specifically for and tested with middle-aged women.

**Objective:**

This study aims to design and implement a web-based intervention intended to reduce alcohol consumption among middle-aged women.

**Methods:**

The study is a 3-arm randomized controlled trial with a web-based intervention plus ecological momentary assessment (EMA) group compared to an EMA-only and a pre-post only control group. The study is aimed at middle-aged women, defined as women aged between 40 and 65 years, who consume alcohol at least weekly or who have consumed 4 or more drinks on 1 occasion in the last month. The intervention aims to reduce alcohol consumption through 4 modules that provide information on the health impacts of alcohol, mindfulness, social influences, and alcohol marketing. Intervention participants will also fill out biweekly EMA assessments. The comparators are EMA-only and pre-post control only. The primary outcome is alcohol consumption at 8 weeks compared between groups. Secondary outcomes are awareness of alcohol-related harms, readiness to change alcohol consumption, health status, mental health, and social support.

**Results:**

Ethics approval for this project was received on September 11, 2019. The trial was registered on August 14, 2020. Recruitment has commenced, and the expected results will be available in 2022.

**Conclusions:**

This web-based intervention aims to reduce alcohol consumption among middle-aged women, a currently understudied cohort in alcohol research.

**Trial Registration:**

Australia New Zealand Clinical Trials Registry (ANZCTR) ACTRN12620000814976; https://www.anzctr.org.au/Trial/Registration/TrialReview.aspx?ACTRN=12620000814976

**International Registered Report Identifier (IRRID):**

DERR1-10.2196/34842

## Introduction

### Background

Historically, men have been larger consumers of alcohol than women, but recent evidence has shown a gender convergence in rates of alcohol consumption [1]. In Australia, this is particularly notable among middle-aged women; rates of long-term risky drinking (measured as 2 or more standard drinks a day) have increased significantly among women aged 40-65 years from 8.8% in 2001 to 11.7% in 2019 [2]. Similarly, rates of risky single-occasion drinking (measured as 5 or more standard drinks on 1 occasion) rose from 13.5% to 19.8% over this same period [2]. This increase is of concern as women are more susceptible to the long-term negative health effects of alcohol including cardiovascular disease, cancer, and diabetes [3]. Women are also more likely to develop alcohol-use disorders from lower levels of consumption than men and are more vulnerable to the neurotoxic effects of alcohol [3].

Several systematic reviews have been carried out to determine the overall efficacy of web-based interventions aimed at reducing alcohol consumption. The most recent, a review of systematic reviews [4], found that web-based interventions were effective in reducing alcohol consumption, albeit effect sizes were mostly small, reflecting a weekly reduction of between 2 and 3 UK units (1 unit=8 grams of ethanol) or between 1 and 2.5 European units (1 unit=10 grams). Studies of interventions that have included women in the sample have often found that higher proportions of women than men take up the intervention [5], suggesting web-based interventions are an appropriate medium for female drinkers. Of studies demonstrating the efficacy of web-based interventions with women, the majority have only included college students [6,7].

There is a specific need for interventions designed by, and targeted at, middle-aged women for several reasons. Firstly, men and women have different patterns of alcohol use and different motives for consumption [3,8,9]. For example, women are lighter drinkers than men, and use alcohol to experience respite from their traditional female domestic and caring responsibilities. Further, most web-based interventions that are female-centric have been aimed at pregnant women or those of childbearing age, with the content heavily tailored to these specific groups and a particular focus on the harms of alcohol to unborn babies [10,11]. Lastly, it has been shown that tailoring interventions using co-design with a target population is particularly efficacious in ensuring the effectiveness of an intervention or program [12,13]; thus, an intervention designed by and for middle-aged women is likely to have amplified effectiveness.

To our knowledge, there are no web-based interventions targeted specifically at middle-aged women that have been documented in the literature. Our study aims to fill this gap by developing and testing the effectiveness of a web-based intervention in reducing alcohol consumption among women aged 40-65 years. The primary aim of this study is to test the effectiveness of a 3-arm web-based intervention in reducing both the frequency of alcohol consumption as well as the alcohol intake per occasion among middle-aged women. Secondary aims include testing the effectiveness of the intervention in increasing awareness of the long- and short-term harms associated with alcohol consumption, increasing motivation to reduce alcohol consumption, reducing alcohol-related harm, improving reported health status and mental health, and increasing social support. We will also test reactivity to the ecological momentary assessment (EMA) by comparing a control group with weekly assessment to a pre-post control group.

### Hypothesis 1

We hypothesize that by the end of the intervention period, participants in the web-based intervention group will report significantly lower alcohol consumption compared with participants in the pre-post control group (H1).

### Hypothesis 2

We hypothesize that by the end of the intervention period, participants in the web-based intervention group will display significant increases in their awareness of harms associated with alcohol consumption (H2a), their motivation to reduce their alcohol consumption (H2b), social support (H2c), and current health status (H2d); they will also display significant decreases in alcohol-related harm (H2e) when compared to the pre-post control only group.

### Hypothesis 3

We hypothesize that by the end of the intervention period, participants in the control group with weekly assessment will have greater reductions in alcohol consumption compared with participants in the pre-post control group (H3a). We further hypothesize that participants in the intervention group will report a greater reduction in alcohol consumption compared with participants in the control group with weekly assessment.

## Methods

### Study Design

This study is a 3-arm randomized controlled trial including 1 intervention group, 1 pre-post control group and 1 control group with weekly assessment. The trial was registered with Australia New Zealand Clinical Trials Registry (ACTRN12620000814976) on August 14, 2020.

### Ethics Approval and Consent to Participate

This study has received ethics approval from the La Trobe University Human Research Ethics Committee (HEC19938). Participants who are eligible for the intervention will be emailed a consent form with brief information about the study, prior to completing the baseline survey. Upon randomization, participants will complete a second short written consent form which will contain information specific to their intervention arm.

### Participants

For this study, participants will be eligible if they are aged between 40 and 65 years, identify as female, reside in the Australian Capital Territory or a surrounding postcode that covers the Australian Capital Territory, are able to understand written English, are able to provide informed consent, own a mobile phone with SMS text messaging capabilities, have access to the internet, and consume alcohol at least weekly or consume 4 or more standard drinks at least once a month.

Women will be ineligible for the study if they are currently receiving treatment for a substance use disorder or are not in Australia for the duration of the study.

### Sample Size Calculation

The effect sizes obtained in brief interventions, that is, change in the intervention group compared to the control group, are usually relatively small [4]. Power analyses in the statistical software G*Power 3.1.9.4 [14] were conducted to determine the power (probability) to successfully find differences between the intervention group and the 2 control groups. In this study, we aim to recruit 3000 participants. However, we may be short on this aim by one-third and have one-third attrition leaving us with a sample of 1333. Using repeated measures ANOVA with within-between interactions (ie, 2 measurements over time [pre-post assessments; note that in any case the EMA assessments will have a higher test power] interacting with the membership in 1 of 3 groups), this reduced sample will still have a power (probability) of more than 99% to detect even small effect sizes (*P*=.99; [15]) with an α-error threshold of .001. In other words, the intended sample size is sufficient to test all hypotheses successfully.

### Recruitment

Recruitment will be carried out through a multipronged approach using both “online” and “offline” access points. Online recruitment will occur through media outlets such as Facebook, Twitter, websites, web-based newsletters, and magazines. Offline recruitment will include advertisements in school newsletters, local community group newsletters, general practitioner clinics, libraries, and gyms. Advertisements will include a link and QR code for a brief web-based screening questionnaire to assess participant eligibility.

We will undertake rolling recruitment, such that participants will be recruited continuously until 3000 individuals are participating in the study. Each participant will undertake the baseline assessment immediately after recruitment to ensure retention.

### Procedures

This study is a 3-arm randomized controlled trial of a web-based intervention to reduce alcohol consumption in middle-aged women.

Potential participants responding to an advertisement will be linked to the study website, which will provide them with a brief description of the study and an eligibility screener. Participants who are eligible will be electronically sent an initial consent form with brief information about the study and will be asked to complete the baseline survey. Participants who do not respond to the initial prompt to complete the baseline survey will be sent 3 reminders over 2 weeks. Upon completion of the baseline survey, participants will be randomized into 1 of 3 groups through the back-end platform specifically designed for the intervention, using a computer-generated number allocated to each participant. Participants will then complete a second short consent form that contains information specific to their intervention arm. As with most behavioral interventions, although it is not possible to blind participants to the procedures relating to their own group, they will not be aware of the procedures relating to the other groups. The researchers responsible for analysis will also be blinded. Only 1 member of the research team, who will be the contact point for any participants experiencing technical difficulties or presenting with queries, will be aware of participant allocation, if required to provide support.

The study will include 3 parallel conditions, of which all 3 will complete a baseline and follow-up questionnaire. The intervention design is shown in Figure 1. Beyond that, the 3 conditions will include the experimental condition (web-based intervention and EMA), and 2 control groups (control group 1: baseline and follow-up assessment only, and control group 2: baseline and follow-up assessment plus EMA). They will undertake assessments of their alcohol consumption over an 8-week period, providing EMA measurements of their alcohol consumption on a twice-weekly basis (measuring their daily alcohol consumption retrospectively). Screenshots of the intervention are shown in Multimedia Appendix 1.

Participants will be able to withdraw from the intervention at their request. If a participant reports an adverse event or complaint, they will be unblinded by matching their participant ID with the contact details database to enable us to establish contact and respond to any issues accordingly. A risk management database will be maintained where records of any issues will be logged.

To promote retention, all participants who complete the study (ie, complete the final assessment measures) will be entered into a draw to win 1 of 24 vouchers. There will be 12 AUD $50 vouchers, 9 AUD $100 vouchers, and 3 AUD $250 vouchers available (AUD $1=US $0.67). The large number of vouchers available reflects the repeated engagement required of participants as well as the intended large number of participants.

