### Comparator

Participants in control group 1 will not be contacted again until the 8-week follow-up questionnaire. Participants in control group 2 (baseline and follow-up assessment plus EMA) will undertake the web-based repeated measures assessment of their alcohol consumption retrospectively twice a week. After they are recruited and randomized, these participants will be sent a link via text message to a web-based EMA. The assessment on Sunday at 12 PM will ask them about their drinking patterns over the weekend (ie, Thursday afternoon until Sunday morning), and the assessment on Thursday at 12 PM will ask about their drinking patterns during the week (ie, Sunday afternoon until Thursday morning). All participants in the control groups will be given access to the web-based intervention at the completion of the study.

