##### Participant’s Use of Intervention (Follow-up)

The intervention’s back-end system will record the number of times participants log in to view the intervention content, and the time they spend on the website each time they log in. It will also record whether participants complete the requested number of follow-up EMAs. These data (number of visits, time spent on website, and number of EMAs completed) will be extracted from the system to assist in assessing the fidelity of the implementation of the intervention.

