### Data Analysis

The reporting and presentation of this trial will be in accordance with the CONSORT (Consolidated Standards of Reporting Trials) guidelines for randomized controlled trials, and data on screening, refusals, and dropout will be coded and reported on per the guidelines [33]. The comparative analysis will be analyzed in accordance with the intention-to-treat principle and the completers-only framework. Participants will have to sign up to the intervention and complete approximately 30% of the EMA surveys to be considered for inclusion in the analysis; missing data will be handled accordingly. The intention-to-treat analyses’ multiple imputation methods will be used, while completers-only analyses will be conducted on participants providing scores for all measurements.

All data that are collected will be analyzed using statistical software packages such as STATA (StataCorp) and Mplus (Muthén & Muthén). ANOVAs, contrasting the intervention groups against both control groups, will be run, and logistic and linear regression models will be used to determine potential influencing variables. Longitudinal analyses will be conducted to test group differences in EMA assessments over time.

Besides testing the main effects of the intervention, moderating effects of age, drinking status (whether participants are “risky” drinkers according to the Australian Alcohol Guidelines [34]), educational status, and presence of dependent children in the household will be investigated to establish whether specific subgroups are more likely to benefit from the intervention.

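### The unqualified claim that the analysts are blinded does not hold for the analysis as described: the EMA-based steps reveal control group 1 even under coded labels

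*Protocol article*

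**What the plan says.** The Procedures section states that "The researchers responsible for analysis will also be blinded". It limits knowledge of allocation to one person: "Only 1 member of the research team, who will be the contact point for any participants experiencing technical difficulties or presenting with queries".

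The same section gives the arms different data. The two controls are "control group 1: baseline and follow-up assessment only, and control group 2: baseline and follow-up assessment plus EMA", and the experimental arm receives the website as well as EMA. EMA runs over 8 weeks, with women "providing EMA measurements of their alcohol consumption on a twice-weekly basis". The Comparator section confirms that the first control arm is left out of this: "Participants in control group 1 will not be contacted again until the 8-week follow-up questionnaire". It also says that the controls receive the website only once the study is complete.

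The Data Analysis section sets a condition for entering the analysis: "Participants will have to sign up to the intervention and complete approximately 30% of the EMA surveys". It then asks for a longitudinal test of group differences in the EMA data. The section on participants' use of the intervention says that the back-end system "will record the number of times participants log in to view the intervention content, and the time they spend on the website". It lists the items to be extracted as "number of visits, time spent on website, and number of EMAs completed" and gives assessment of fidelity as their purpose.

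The article does not say which analyses the blinding covers.

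**The concern.** The arms differ in which records exist, not only in the values recorded. Replacing arm names with codes hides nothing once the analyst works with a variable that is empty by design in one arm. Two steps in the Data Analysis section, the EMA completion threshold and the EMA group comparison, require such a variable.

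The arm exposed is an important one. Hypotheses 1 and 2 compare the intervention with the pre-post control group, and Hypothesis 3a compares the EMA-only arm with it. Participants know their own procedures, and the outcomes are self-reported. Analyst blinding is therefore a relevant guard over choices that the article leaves loose: how strictly to apply an approximate 30% threshold, how to impute, and which of the ANOVA and regression models to emphasise. If a trial report repeated the sentence unchanged, it would claim a protection that the described workflow does not provide.

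**Working it through.** The plan gives no figure for this point, so the check sets the data that each arm produces against the data that the analysis uses.

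**Data by arm** (Procedures; Comparator; Participant's Use of Intervention)

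| Arm | Baseline and 8-week questionnaires | EMA surveys scheduled | Log-ins to content during the 8 weeks |
|---|---|---|---|
| Control group 1 | yes | 0 | none |
| Control group 2 | yes | 2 per week × 8 weeks = 16 | none |
| Intervention | yes | 2 per week × 8 weeks = 16 | possible |

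**Step 1: the inclusion threshold.** 30% of 16 is 0.30 × 16 = 4.8, or about 5 surveys. No woman in control group 1 can reach it. Whoever applies the rule must either exempt that arm, which requires knowing which arm it is, or see one coded arm fail completely.

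**Step 2: the EMA group comparison.** Only two of the three arms have EMA data. A model of group differences in EMA over time contains two codes, and the missing code is control group 1.

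**Step 3: could coded labels survive by chance?** The sample-size section's reduced sample is 1333. Assuming equal allocation, this is 1333 / 3 ≈ 444 women per arm. An EMA arm would look like control group 1 only if none of its women answered a single survey. If a share q never respond, independently of one another, that probability is q^444. The article gives no value for q, so a range is shown:

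- q = 0.3: about 7 × 10⁻²³³
- q = 0.9: about 5 × 10⁻²¹

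At arm level, identification of control group 1 is practically certain.

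**Step 4: individual women.** A woman in an EMA arm who never responds looks like a member of control group 1. The expected number per EMA arm is 444 × q, which is about 44 at q = 0.1, 133 at q = 0.3 and 400 at q = 0.9. How many women can be placed from their own records therefore depends on engagement, which the article does not report.

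**Step 5: the other two arms.** Both have 16 scheduled surveys, so EMA counts by design do not tell them apart. Log-ins during the 8 weeks would do so at group level, but only if usage data are merged into the analysts' file. The article does not say that they are.

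**Step 6: what can stay masked.** All three arms complete the baseline and follow-up questionnaires. A comparison built only from those items contains nothing that is empty by design in one arm.

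**The case against.** The best defence is that the article assigns these tasks to nobody in particular. The usage data are described in the passive and tied to fidelity. The Data Analysis section does not say who applies the 30% rule. The one team member who may know allocation could do both. The primary comparison at 8 weeks uses questionnaires common to all arms and could be run on coded groups, and a condensed article may leave such file handling to another document.

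Much of this stands, and it rules out stronger readings that a reader might infer:

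- **That all three arms are exposed.** EMA data alone reveal only control group 1. Separating the other two needs usage data, and the article does not give these to the blinded analysts.
- **That nearly every woman's allocation is visible.** This would need an adherence figure, which the article does not give (step 4).
- **That any content log-in marks an intervention participant.** Controls gain access at study completion and recruitment is rolling, so this is safe only for log-ins within the 8 weeks.
- **That a blinded analysis is impossible, or that nothing else protects the trial.** The pre-post comparison can be masked. Trial registration, allocation by the platform after the baseline survey, and a planned intention-to-treat analysis with multiple imputation are also in place.

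The defence does not remove the core. The threshold and the EMA comparison are stated in the article itself and are not details left to another document. Handing the threshold to an unblinded colleague does not help if the analysts then receive an inclusion flag, because the flag would be negative throughout control group 1 or would treat that arm differently.

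**Conclusion.** The concern holds in limited form. The article makes an unqualified claim of analyst blinding and also describes two analysis steps that reveal control group 1 under any coding of the arms. Scheduled EMA surveys are 0, 16 and 16, and the threshold of about 5 cannot be met in the first arm. If usage data from the 8 weeks are merged too, the intervention arm and control group 2 become distinguishable at group level.

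This rests on the arms being run as the Procedures and Comparator sections describe, and on the same analysts handling the EMA data. Equal allocation and independent non-response are assumed only for the illustration in step 3. It does not follow that the primary result would be biased. What follows is that the blinding statement needs a stated scope and a workflow that delivers it. Whether a 30% EMA threshold is a suitable definition of the analysis set is a separate question.

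**What to change.** Split the analysis into two steps and describe them in the article.

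1. **Blinded step.** The team member who may know allocation prepares an extract of all randomised women. It contains only baseline and 8-week items asked of every arm, with scrambled arm codes. It holds no EMA data, no usage data, and no EMA-based inclusion rule or flag. Any follow-up item not put to all three arms stays out; the article does not say which arms answer the satisfaction questionnaire, so this needs checking. The analysts derive, impute and analyse the outcomes, running all three pairwise contrasts so that the named hypotheses can be read off once labels are attached. Code and output are then locked.
2. **Unmasked step.** The codes are opened, and the EMA and usage data are merged for the EMA-threshold, longitudinal and fidelity analyses. Usage data are cut off at the end of each woman's 8 weeks.

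Amend the Procedures section to say that blinding of the analysts covers the first step only.

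The cost is a second data extract from the existing back-end, with no extra staff or data collection. The real downside is that EMA data cannot serve as auxiliary variables for imputation in the blinded step. They can be used that way only in a later sensitivity analysis.
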